### Primary outcome

The primary endpoints of the study are HbA1c and antidiabetic medication dosage. These primary endpoints will be combined to compare the total successful outcomes between the FMD group and the control group after 12 months of follow up. A successful outcome will be defined as any reduction in the antidiabetic medication dosage and/or a decrease of HbA1c of 5 mmol/mol or more. HbA1c and antidiabetic medication dosage will also be recorded after 6 months.

### Secondary outcomes

Bodyweight, waist circumference, body mass index and body fat percentage: recorded at baseline and every following study visit.Blood pressure: systolic and diastolic values measured at baseline and every following study visit.Fasting glucose: measured at baseline, after 6 months and after 12 months.Glucose and insulin response to an oral glucose load: OGTT measured at baseline, after 6 months and after 12 months.Plasma lipid profiles: measured at baseline, after 6 months and after 12 months.Metabolomics: measured at baseline and after 12 months.High sensitive CRP: measured at baseline, after 6 months and after 12 months.Dosage of statins and antihypertensive medication: recorded at baseline, after 6 months and after 12 months.Visceral fat, liver/heart ectopic fat, total body fat: from magnetic resonance imaging, measured at baseline, after 6 months and after 12 months.Cardiovascular function: from magnetic resonance imaging, measured at baseline, after 6 months and after 12 months.Gut microbiota architecture: measured from stool samples stored at baseline, after 1 week, after 6 months and after 12 months.Change in dietary pattern: DHD-FFQ measured at baseline, after 6 months and after 12 months [25].Cost-effectiveness analysis: The economic evaluation will consist of both a trial-based cost-effectiveness analysis with a time horizon of 12 months and a model-based cost-utility analysis with a lifetime horizon.Change in physical activity: SQUASH measured at baseline, after 6 months and after 12 months [26].Quality of life: EQ-5D-5L measured at baseline, after 3 months, after 6 months, after 9 months and after 12 months [27, 28].Treatment satisfaction: DTSQs at baseline, after 3 months, after 6 months, after 9 months and after 12 months [29]. DTSQc after 12 months [30].Feasibility in clinical practice: Percentage of fully compliant participants after 12 months, where compliance is based on self-report and laboratory measures. Glucose levels and finger-stick ketone bodies tests are performed after several FMD periods.

### Power calculation

The number of participants that will be included in the study is limited to 100 (50 in each group). We computed expected effect sizes with a sample size of 100. As all participants will be asked to come in for T8, we work with a limited loss to follow-up of 10% [8], thus basing the calculations on 90 participants (45 in each group).

We computed the effect size that can be detected with 80% power for the binary endpoint, which is equal to one if either a lower dose of antidiabetic medication is used at the end of the study compared to the start, if HbA1c is at least 5 mmol/mol lower at the end compared to study start, or both.

The expected percentage of participants in the control group who will reach this endpoint is between 4 and 6% [8, 31]. For this power calculation, we assumed a percentage of 5% of participants in the control group who will reach the combined endpoint. With a significance level of 5 and 80% power, using a two-sided binomial test with 45 participants in each group, an absolute difference in percentages of 21% (i.e. 5% in the control group and 26% in the treatment group) can be detected.

### Statistical analysis

Data will be analysed on an intention-to-treat basis at the 12-month point. In addition, a per protocol analysis well be carried out. A significance level of 5% will be used.

### Baseline data

Baseline data from the two groups will be compared on the following baseline values: age, gender, BMI and metabolic parameters. The values will be summarized using mean and standard deviation, or in case of an asymmetric distribution, by using median and interquartile range.

Hypothesis tests will be carried out using t-tests for independent samples, or, if the assumption of normality is violated, with a Mann-Whitney test. Multiple testing will be corrected for by using the Benjamini-Hochberg procedure. If the groups are found to be imbalanced on one or more covariates, then the following analyses will be adjusted for those covariates. Furthermore, the following analyses will be adjusted for gender and for weight < 100 kg or > 100 kg, since randomization is stratified for these values.

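### Beyond the two stratification factors, covariates are chosen by corrected baseline significance tests, so baseline HbA1c would rarely be adjusted for and moderate chance imbalances would mostly stand

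*Protocol article*

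**What the plan says.** The Baseline data section of the protocol article contains two adjustment rules.

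- **Conditional rule.** "Baseline data from the two groups will be compared on the following baseline values: age, gender, BMI and metabolic parameters". The method follows: "Hypothesis tests will be carried out using t-tests for independent samples, or, if the assumption of normality is violated, with a Mann-Whitney test", and then "Multiple testing will be corrected for by using the Benjamini-Hochberg procedure". The consequence is "If the groups are found to be imbalanced on one or more covariates, then the following analyses will be adjusted for those covariates". No other definition of imbalance is given, so the corrected test is the natural reading.
- **Fixed rule.** The next sentence needs no test: "Furthermore, the following analyses will be adjusted for gender and for weight < 100 kg or > 100 kg, since randomization is stratified for these".

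The Statistical analysis section sets the level: "A significance level of 5% will be used". No separate level is given for the baseline tests.

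The section Primary and secondary outcomes compares HbA1c and antidiabetic medication dosage between arms on their 12-month values. Neither baseline HbA1c nor baseline medication is named as a fixed covariate. Metformin use is not named in the list of baseline variables and is not a stratification factor.

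**The concern.** Allocation is computer-generated and concealed, so any baseline difference between arms arose by chance. A baseline significance test therefore examines a null hypothesis already known to be true. Its result says nothing about whether adjustment would help; that depends on how strongly the covariate predicts the outcome. The multiplicity correction raises the bar further, in a setting where a missed imbalance is the costlier error.

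Two covariates matter most. Baseline HbA1c is likely to predict 12-month HbA1c, yet it enters that comparison only if flagged. Baseline metformin use bears on 12-month dosage. It also bears on the composite: participants on lifestyle advice alone are eligible, and someone taking no drug at the start cannot be on a lower dose at the end.

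At stake are the precision of these comparisons, their validity given the imbalance actually seen, and knowing the model before the data are seen.

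**Working it through.** **Inputs from the protocol article.** 50 per arm randomised; 45 per arm in the power calculation; 5% level; Benjamini-Hochberg over the baseline tests.

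**Assumptions, because the article gives no figure.** Number of baseline tests m = 4 to 15; correlation between those variables 0 to 0.6; correlation r between baseline and 12-month HbA1c = 0.3 to 0.7.

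**1. The plan's own figure.** The article states no figure for the covariate rule. Its power statement (5% vs 26%, 45 per arm, 80%) reproduces with the pooled normal approximation. The mean proportion is 0.155. The null SE is √(2 × 0.155 × 0.845 / 45) = 0.0763 and the alternative SE is √((0.05 × 0.95 + 0.26 × 0.74) / 45) = 0.0730. Then (0.21 − 1.96 × 0.0763) / 0.0730 = 0.83, giving power of 79.6%. This figure does not depend on the covariate rule and is unaffected.

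**2. Difference needed to be flagged.** The SE of a standardised difference at 50 per arm is √(2/50) = 0.20. A covariate flagged alone must reach t(98 df, 1 − 0.05/(2m)) × 0.20:

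| m | Difference needed (SD) |
|---|---|
| 1 (no correction) | 0.40 |
| 4 | 0.51 |
| 10 | 0.57 |
| 15 | 0.60 |

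**3. How often the rule acts.** In 200,000 simulated randomisations per scenario (m = 4 to 15, correlation 0 to 0.6), at least one covariate is flagged in about 3.8% to 5.0% of trials. One given covariate is flagged in about 0.4% to 1.8%.

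**4. How often there is something to miss.** P(|difference| > 0.3 SD) = 2 × P(Z > 0.3/0.20 = 1.5) = 13.4%. P(> 0.4 SD) = 2 × P(Z > 2.0) = 4.6%. Given a difference above 0.3 SD, the rule flags it in about 4% to 5% of cases (8 to 12 independent tests). Given one above 0.4 SD, it flags it in about 8% to 40% (m = 4 to 15).

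**5. Effect on the unadjusted 12-month HbA1c test at a given imbalance d.** The comparison shifts by r × d. With 45 per arm the SE is √(2/45) = 0.2108, the critical difference is 1.96 × 0.2108 = 0.413, and the conditional SD is √(1 − r²) × 0.2108. For d = 0.4 and r = 0.6: shift 0.24, conditional SD 0.169, (0.413 − 0.24)/0.169 = 1.03, so conditional type I error is 15.2%.

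| d (SD) | r = 0.5 | r = 0.6 | r = 0.7 |
|---|---|---|---|
| 0.2 | 4.6% | 4.2% | 3.5% |
| 0.3 | 7.6% | 8.4% | 8.9% |
| 0.4 | 12.2% | 15.2% | 18.8% |
| 0.5 | 18.6% | 25.1% | 33.7% |

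**6. Averaged over all imbalances above 0.3 SD, with the rule applied** (simulated null trials, 50 per arm). Conditional type I error is about 6–8% for r = 0.3, 11–12% for r = 0.5 and 14–19% for r = 0.6–0.7. With routine adjustment it is about 5% throughout.

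**7. Overall type I error.** At r = 0.6–0.7 the other 87% of trials run at about 2.5% to 3.2%. Weighting: 0.13 × 15% + 0.87 × 3.2% = 4.7%; 0.13 × 19% + 0.87 × 2.5% = 4.6%. Direct simulation gave about 4.4% to 5.2%. There is no overall inflation.

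**8. Precision forgone.** Adjusting for baseline multiplies residual variance by 1 − r²: 0.91, 0.75, 0.64 and 0.51 for r = 0.3, 0.5, 0.6 and 0.7.

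**The case against.** Several points on the other side stand.

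- A reader might infer from the conditional sentence that nothing is adjusted for unless a test flags it. The next sentence rules that out: gender and weight stratum are always in.
- A reader might infer that even strong imbalance goes uncorrected. Differences above about 0.6 SD would nearly always be flagged; the gap lies mainly at about 0.3 to 0.5 SD.
- A reader might take the conditional error rates as a failure of the trial's error control. They are not: averaged over randomisations the rate stays near 5%.
- The composite, on which the power calculation rests, is defined by change from each participant's own baseline. The mixed models for repeated outcomes can also use the baseline visit, although the article does not say whether it enters as an outcome. The calculation above covers neither.
- The size depends on r, which may be weakened because GPs may adapt medication towards an HbA1c target in both arms.
- The metformin point is not quantified.

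None of this supports the baseline test as a way of choosing covariates. The fixed factors do not include baseline HbA1c or medication, and the 12-month HbA1c and dosage comparisons take no account of baseline unless the screen happens to fire. Nor can the rule be treated as a detail left to an analysis plan: the article states it.

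**Conclusion.** The point holds in a limited form. Apart from gender and weight stratum, covariates enter only through a corrected baseline significance test. For any one covariate that screen fires in about 0.4% to 1.8% of trials (4 to 15 tests assumed), so most moderate imbalances would go unadjusted.

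The consequences are lost precision, bias conditional on the imbalance observed, and a model partly unknown until the data are in. They fall mainly on the 12-month HbA1c and dosage comparisons. The size is computed for HbA1c only and rests on the assumed r; at r = 0.3 the conditional excess is small. The documents do not support a claim of inflated overall type I error, and neither the sample size nor the detectable difference changes. This should be corrected, but it does not threaten the trial's validity.

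**What to change.** In Baseline data, delete the hypothesis tests, their Benjamini-Hochberg correction and the conditional-adjustment sentence, and present baseline data descriptively. Keep the adjustment for gender and weight stratum as it stands. Add two prespecified covariates: the baseline value of the outcome, and baseline metformin use (yes/no).

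In Primary and secondary outcomes, name a model that can carry these covariates, for example ANCOVA for 12-month HbA1c, since a two-sample t-test or Mann-Whitney test cannot.

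The cost is wording only. HbA1c and medication dosage are already recorded at baseline in the assessment schedule (Table 2), and no sample-size figure changes. The change should be made before outcome data by arm are examined.

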### Primary and secondary outcomes

Primary and secondary outcomes will be summarized using mean and standard deviation, or in case of an asymmetric distribution, by using median and interquartile range. HbA1c and antidiabetic medication dosage will be compared between the two groups, using t-tests for independent samples, or, if the assumption of normality is violated, with a Mann-Whitney U test. The values at 12 months will be used for these tests.

To compare the total successful outcomes, the primary endpoints HbA1c and antidiabetic medication dosage will be combined. A successful outcome will be defined as any reduction in the antidiabetic medication dosage and/or a decrease of HbA1c of 5 mmol/mol or more. This will be compared between the two groups as described above. To correct for multiple testing, the procedure of Benjamini-Hochberg will be used.

To detect a difference in the profiles of the outcomes that are measured repeatedly during the course of the study, a mixed model will be used. This model can be used if there is missing data, and if participants have their visits at different time points. The interaction between time and treatment arm will be included. Besides a random slope per participant, a random intercept and the inclusion of splines will be considered. In case complete observations are available for at least 80% of the participants, and if the pattern of missing observations is deemed noninformative, the mixed model will be compared to a generalized least squares model with unstructured, compound symmetry, or AR (1) covariance structures. The choice between the options will be made using the AIC criterion.

As multiple primary endpoints are measured repeatedly, multiple mixed models will be fit. For each of the models, the outcome of the global F or LR test (where appropriate) will be reported, and significance evaluated using the procedure of Benjamini-Hochberg.

The secondary outcome ‘feasibility in practice’, measured as the percentage of compliant participants, will not be tested, as there is no reference value for comparison.

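### The tests named for the primary outcomes cannot carry the promised stratum adjustment, leave out baseline HbA1c and dosage, and are not ranked against the planned mixed models

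*Protocol article*

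**What the plan says.** All references are to the protocol article.

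- **Primary and secondary outcomes (Statistical analysis):** "HbA1c and antidiabetic medication dosage will be compared between the two groups, using t-tests for independent samples", with Mann-Whitney U as the fallback, applied to the values at 12 months. The composite success endpoint (any dose reduction, an HbA1c fall of at least 5 mmol/mol, or both) follows with "This will be compared between the two groups as described above". The only tests described up to that point are the t-test and Mann-Whitney.
- **Baseline data:** "Furthermore, the following analyses will be adjusted for gender and for weight" stratum, because randomisation is stratified on both. Covariates found imbalanced in baseline hypothesis tests, corrected by Benjamini-Hochberg, are to be adjusted for as well.
- **Power calculation:** the composite is powered "using a two-sided binomial test with 45 participants in each group", giving a detectable contrast of 5% versus 26%.
- **Primary and secondary outcomes, further on:** mixed models with a time-by-arm interaction are planned for repeatedly measured outcomes, including the primary endpoints. Their global test is to be reported. Nothing says whether these models or the 12-month tests decide the primary question.
- **Table 2:** HbA1c and medication dosage are recorded at baseline, 6 months and 12 months.

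**The concern.** An independent-samples t-test and a Mann-Whitney test compare two groups and take no covariates. An analyst following Primary and secondary outcomes breaks the promise made under Baseline data, and one who keeps that promise must replace the named tests. The composite has a further mismatch: one section powers it with a test for proportions, and another points it to tests meant for continuous or ordinal data. This is a conflict between statements on the page, so it is not a matter of detail left to an analysis plan.

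The HbA1c and dosage tests also discard the baseline measurement. Study population admits patients on lifestyle advice alone as well as patients on metformin, so starting dosage differs by design. The sample is capped at 100, so precision lost in the analysis cannot be bought back by recruiting. With adjusted and unadjusted routes both open and no decisive one named, the choice could be made after the results are seen.

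**Working it through.** **1. The plan's own figure.** Inputs from Power calculation and Statistical analysis: 45 per arm, 5% versus 26%, two-sided 5%, 80% power. Pooled two-proportion z-test:

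- Mean rate = (0.05 + 0.26)/2 = 0.155.
- SE under the null = √(0.155 × 0.845 × 2/45) = 0.0763.
- SE under the alternative = √((0.05 × 0.95 + 0.26 × 0.74)/45) = 0.0730.
- Power = Φ((0.21 − 1.96 × 0.0763)/0.0730) = Φ(0.828) = 79.6%. The matching sample size is 46 per arm against 45 stated.

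The stated 21-point difference reproduces.

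**2. Does the misnamed test harm the composite?** Exact enumeration of all 45 × 45 outcomes:

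| Test | Power, 5% vs 26% | Type I error, both arms 5% |
|---|---|---|
| t-test on 0/1 data | 84.1% | 4.9% |
| Mann-Whitney, no continuity correction | 83.6% | 4.1% |
| Pearson chi-square | 84.1% | 4.9% |
| Fisher's exact | 74.6% | 0.6% |

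The t-test and Mann-Whitney behave almost like chi-square. Fisher's exact test differs clearly, which is a reason to name the test family.

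**3. Cost of leaving out baseline HbA1c.** The article gives neither an SD for HbA1c nor a baseline-to-12-month correlation r. Results are therefore in SD units, with r = 0.3 to 0.7 as an assumption.

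- Unadjusted detectable difference = (1.96 + 0.84) × √(2/45) = 0.59 SD.
- ANCOVA multiplies this by √(1 − r²).
- Equivalent unadjusted trial size = 90/(1 − r²).
- The last column is power at a true difference of 0.59 SD, where the unadjusted test has 80% (normal approximation).

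| r | √(1 − r²) | SE cut | Detectable difference | Equivalent analysed N | Power at 0.59 SD |
|---|---|---|---|---|---|
| 0.3 | 0.954 | 5% | 0.56 SD | 99 | 83.6% |
| 0.5 | 0.866 | 13% | 0.51 SD | 120 | 89.9% |
| 0.7 | 0.714 | 29% | 0.42 SD | 176 | 97.5% |

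**4. Chance imbalance.** A baseline difference of d SD shifts the unadjusted 12-month difference by r × d. For d = 0.2 the shift is 0.06 SD (r = 0.3) to 0.14 SD (r = 0.7).

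**5. Number of events for the composite.** 45 × 0.05 + 45 × 0.26 = 2.25 + 11.7, or about 14. That is few for a regression with several covariates, but workable for a Mantel-Haenszel estimate over the four gender-by-weight strata.

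**The case against.** The strongest reply is that the plan already contains a baseline-using analysis. The mixed models cover the repeatedly measured primary endpoints, can take covariates and tolerate missing visits. This stands, and it narrows the criticism: the tool is there, but it is presented as an analysis of profiles beside the 12-month tests, without an order between them.

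The plan also does not ignore baseline altogether. The composite is defined by change from baseline, so omission of baseline is a criticism of the separate HbA1c and dosage tests only. The imbalance rule could bring baseline HbA1c in as a metabolic parameter, but only if a multiplicity-corrected significance test flags it, and the named tests could not carry it even then.

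The gain may be modest. Usual care lets GPs adapt medication towards an HbA1c of 53 mmol/mol in both arms, which could weaken the correlation. At r = 0.3 the SE falls by only 5%.

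Three stronger readings may tempt a reader and are not supported:

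- **Inflated false-positive rate.** Given a 0.4 SD baseline imbalance, the unadjusted test's conditional type I error would be 12 to 19% (r = 0.5 to 0.7). An imbalance that large, in either direction, has only about a 6% chance with 45 per arm (0.4/√(2/45) = 1.90). Averaged over randomisations the error is not inflated, and ignoring stratification factors makes these tests conservative.
- **Low power for a 5 mmol/mol mean difference.** The 5 mmol/mol in Primary outcome is a cut-off for an individual's success. The plan sets no between-group target for mean HbA1c.
- **A breach of intention to treat.** The plan states that "Data will be analysed on an intention-to-treat basis", Participant withdrawal asks those who withdraw to return at T4 and T8, and the mixed model accepts gaps. Further imputation detail may properly sit in an analysis plan that is not shown.

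**Conclusion.** The point holds as one of internal consistency and precision, and it should be fixed. Power calculation, Baseline data, and Primary and secondary outcomes name procedures that cannot all be applied to the same primary endpoints, and no analysis is named as decisive.

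For HbA1c, the unadjusted 12-month test forgoes a 5 to 29% reduction in standard error, if the baseline-to-12-month correlation lies between 0.3 and 0.7 and 45 per arm are analysed. The range is an assumption; the direction is not in doubt for any non-trivial correlation. For the composite, the numerical harm of the misnamed test is negligible. What is lost there is the promised stratum adjustment and agreement with the power calculation, whose 5% versus 26% statement remains valid.

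**What to change.** Reconcile the three passages and name one decisive analysis per primary outcome:

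- **HbA1c:** ANCOVA at 12 months, or the 12-month contrast from the mixed model already planned, adjusted for baseline HbA1c, gender and weight stratum. State which of the two it is.
- **Dosage:** the same, with baseline dosage as covariate, where a common dose scale exists. Lifestyle-only patients start at zero and Medication use allows a second drug class, so the scale needs stating.
- **Composite:** a Mantel-Haenszel risk difference over the gender-by-weight strata, with the same test family named in Power calculation and in Primary and secondary outcomes.
- **Sensitivity:** keep the t-test or Mann-Whitney comparison in this role.

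The cost is wording in the statistical section and a little more analysis work. No new data, visits or participants are needed.

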### Cost-effectiveness analysis

The economic evaluation will consist of both a trial-based cost-effectiveness analysis with a time horizon of 1 year and a model-based cost-utility analysis with a lifetime horizon.

In the trial-based economic evaluation, the effects of the FMD will be compared to usual care and related to the difference in costs. Differences in mean costs and effects (HbA1c -level and QALYs) between strategies will be compared with two-sided bootstrapping. In a net-benefit analysis, costs will be related to the participant reported outcomes and presented in a cost-effectiveness acceptability curve. No discounting will be applied due to the time horizon of the economic evaluation of 1 year. Multiple imputation will be used for handling missing data. The evaluation will be performed from a healthcare and societal perspective. Sensitivity analysis will be carried out for the most important assumptions.

In the model-based cost-utility analysis the UKPDS Outcomes model will be used to estimate lifetime costs and QALYs for the FMD in comparison to usual care [32]. In this lifetime cost-utility analysis costs will be discounted at a percentage of 4% and effects at a percentage of 1.5%, according to the Dutch guidelines for health economic research [33]. Sensitivity analysis will be carried out for the most important input parameters.

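### The 12-month tests, above all the powered binary composite, can as written include only participants with a 12-month value, although the analysis is called intention-to-treat

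*Protocol article*

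**What the plan says.** Under Statistical analysis: "Data will be analysed on an intention-to-treat basis at the 12-month point". Under Primary and secondary outcomes, HbA1c and antidiabetic medication dosage are compared by t-test or Mann-Whitney U test, and "The values at 12 months will be used for these tests". The composite (any dose reduction, or an HbA1c fall of at least 5 mmol/mol, or both) is then compared by reference back to those tests. No rule is given there for a participant without a 12-month value.

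Under Power calculation, 100 are randomised and 10% are expected to be lost, "thus basing the calculations on 90 participants (45 in each group"). That section gives the recall of all participants at T8 as the reason for assuming so little loss. Participant withdrawal adds that those who withdraw are asked back at T4 and T8 so that intention-to-treat analysis is possible.

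Missing data are addressed in two places. The mixed models for repeatedly measured outcomes, which extend to the primary endpoints, are said to be usable when data are missing. In the Cost-effectiveness analysis section, where the effects are HbA1c level and QALYs, "Multiple imputation will be used for handling missing data".

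**The concern.** A two-sample test on 12-month values has nothing to enter for a participant who has none. Unless a rule is added, the composite will in practice be tested on those who attended T8, which is narrower than everyone randomised. The article deals with missing data for the profile models and for the economic evaluation, but not for the one endpoint in the power calculation.

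Participants know their allocation and the diet is demanding. It is plausible, though not established, that those who stop and do not return are more often diet-arm participants without a response. Leaving them out would raise the success rate in that arm and overstate the benefit. There is also a consistency problem: HbA1c could be reported with imputation in the economic evaluation and without it in the 12-month clinical test, giving two HbA1c differences on different sets of participants.

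**Working it through.** **1. The plan's own figure.** Inputs from Power calculation: 45 per arm, 5% v 26%, two-sided 5%. Pooled normal approximation, with mean rate 0.155:

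- z = [0.21·√45 − 1.96·√(2·0.155·0.845)] / √(0.05·0.95 + 0.26·0.74)
- = (1.409 − 1.003) / 0.490 = 0.83, so power is 79.6%.

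Solving for 80% gives a detectable difference of 21.1 points. The stated 21 points reproduces on 45 per arm. With all 50 per arm observed, power at 5% v 26% would be 83.7%. The power figure is not in error.

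**2. Loss that depends on the 6-month response (assumed).** True rates are 26% and 5%. In the diet arm, T4 non-responders are lost at 20% and T4 responders at 5%. In the control arm 5% are lost at random, so its rate stays at 5%. Let a and b be the proportions of eventual successes and eventual failures who had responded at T4. The retained fractions are:

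- successes: kS = 0.95a + 0.80(1 − a)
- failures: kF = 0.95b + 0.80(1 − b)
- observed diet-arm rate = 0.26·kS / (0.26·kS + 0.74·kF)

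| a | b | kS | kF | Observed rate | Bias (points) | Total lost |
|---|---|---|---|---|---|---|
| 0.50 | 0.20 | 0.8750 | 0.8300 | 0.2275/0.8417 = 27.0% | +1.0 | 7.9 + 2.5 = 10.4 |
| 0.55 | 0.10 | 0.8825 | 0.8150 | 0.2295/0.8326 = 27.6% | +1.6 | 8.4 + 2.5 = 10.9 |

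Total loss is close to the planned 10. Here loss depends only on arm and T4 response, so imputation that uses both removes the bias in expectation.

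**3. Extreme case (assumed).** All 10 lost are failures, 8 on the diet and 2 controls. Expected successes are 0.26·50 = 13 and 0.05·50 = 2.5.

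- Observed: 13/42 = 30.95% and 2.5/48 = 5.21%, a difference of 25.7 points.
- Missing counted as failure: 13/50 − 2.5/50 = 21 points.

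**4. No true effect.** Failures are lost at 20% on the diet and 5% in control (assumed), with 50 per arm. At success rate p the expected bias is p/[p + 0.80(1 − p)] − p/[p + 0.95(1 − p)]. At 5% this is 0.05/0.81 − 0.05/0.9525 = 0.9 points. Simulation with 400,000 trials and a pooled z test:

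| Success rate, both arms | Bias (points) | Two-sided rejection | Favouring the diet |
|---|---|---|---|
| 5% (planned control rate) | +0.9 | 4.6% | 3.5% |
| 6% (top of the planned range) | +1.1 | 5.1% | 3.9% |
| 25% (not a planning value) | +3.4 | 6.7% | 5.7% |

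Without loss, the 5% row gives 4.3% two-sided and 2.2% favouring the diet.

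**5. How much the rule matters.** If the observed rates were 26% v 5% and missing counted as failure over 50 per arm, the difference would be:

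- 5 lost per arm: 23.4% − 4.5% = 18.9 points
- 8 diet, 2 control: 21.8% − 4.8% = 17.0 points
- 10 diet, 0 control: 20.8% − 5.0% = 15.8 points
- 0 diet, 10 control: 26.0% − 4.0% = 22.0 points

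**The case against.** The strongest reply is that the article never says participants without a value are excluded. The sentence on 12-month values can be read as fixing the time point only. Intention-to-treat is promised, withdrawn participants are called back, and a full protocol or analysis plan, not shown here, may hold the rule. All of this is fair, and it rules out the harsher reading that the plan openly defines a completers analysis under a false label. The narrower point stands: the tests named need a 12-month value, and the expected 10% loss is what remains after the recall.

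Four further inferences are tempting and are not supported.

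- The 90 is an ordinary allowance for attrition in the power calculation. It is not a defined analysis set.
- The 6-month data are not unused. The mixed models for HbA1c and dosage use them and tolerate missing values. They compare profiles over time, however, and no model for a binary outcome is named, so the composite is not clearly covered.
- Imputation is not limited to costs and QALYs, because HbA1c is one of the economic effects.
- A materially raised type I error appears only at success rates such as 25% in both arms. At the protocol's 5% the two-sided rate stays below nominal, and only the balance between the tails shifts.

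The direction of bias is also not known. The documents give no information on who will be lost, and loss concentrated in control failures would work the other way.

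**Conclusion.** The concern holds for the 12-month two-sample tests and matters most for the composite. As written, these tests can use only participants with a 12-month value, which does not deliver the intention-to-treat analysis the article promises once some values are missing. The likely consequence is a modest overstatement of the difference, about 1 to 1.6 points when loss follows the 6-month response. The shift from 21 to 25.7 points is an extreme case. Both rest on assumed loss patterns with more diet-arm non-responders lost. The effect on false positives at the planned rate is small: about 3.5% in the tail favouring the diet against a nominal 2.5%, with no two-sided inflation. The point is worth correcting because the remedy is cheap and the choice of rule can move the estimate by several points.

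**What to change.** Extend the multiple imputation already planned for the economic evaluation to 12-month HbA1c and antidiabetic medication dosage. Use arm, gender, weight stratum and the T0 and T4 values as predictors. Derive the composite within each imputed dataset, analyse all 100 participants as randomised, and combine the results. Use the same imputed HbA1c in the clinical and the economic comparisons so that the two agree. Add one sensitivity analysis counting missing as failure, since imputation from T4 only partly corrects loss that depends on the 12-month outcome itself. Fix the rule before 12-month data are examined by arm.

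The cost is a little more analysis work. T4 HbA1c and dosage are already in the assessment schedule, so no new data are needed. Reported success rates may be slightly less favourable than among attenders alone.
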